The effectiveness of reminiscence therapy has been investigated by several meta-analyses [6, 9–13]. Pinquart *et al*. [13] analyzed 57 controlled studies, of which eight compared reminiscence with a control condition. Reminiscence was associated with a large effect size (d =1.00), comparable with cognitive behavioral therapy (CBT). These findings lead the authors to conclude that reminiscence and CBT are effective modalities of treatment for depression in older adults. A more recent review by Pinquart and Forstmeier [6] aggregated results of 128 selected studies. Findings showed that reminiscence interventions produced small to moderate improvements of depressive symptoms (g =0.57) and of other indicators of mental health, such as ego integrity (g =0.50), purpose in life (g =0.73), and death preparation (g =0.52). In addition, it was found that improvements of depression were greater than improvements of positive mental health and cognitive performance. With respect to moderator variables, results of this meta-analysis showed that life-review therapy had stronger effects on depression than either life review or simple reminiscence. However, this effect was explained by higher levels of depression symptoms in life-review patients at pre-test. There was no significant difference between the one-to-one and group formats. In addition, the number of sessions had no moderating effects.

In summary, the findings of previous meta-analytic studies indicate that reminiscence therapy is a promising non-pharmacological approach to improve mental health in elderly individuals. However, more randomized controlled trials are needed to assess the effectiveness of this strategy and its specific benefits for institutionalized seniors [14].

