## Methods/Design

### Aim of the study

Based on the need for further randomized controlled trials in this area, the present study aims at assessing the effects of group reminiscence on psychosocial wellbeing in institutionalized, non-demented elderly individuals. First, we will examine the specific effects of simple reminiscence as compared to a placebo intervention in which participants are engaged in everyday conversations (discussion of current events). The findings of previous meta-analyses are inconclusive on this issue. The review carried out by Bohlmeijer *et al*. [9] found no significant differences between studies that used an active placebo and those that used a wait-list condition. In contrast, the Pinquart and Forstmeier meta-analysis [6] observed larger improvements in positive wellbeing if the control condition received no intervention as compared to standard conversation, indicating that socialization activities can also bring about positive emotional states.

Second, we intend to assess the impact of reminiscence on a broad range of psychosocial outcome indicators, including depression symptoms, positive wellbeing (self-esteem, life satisfaction), and quality of life. Since we aim to evaluate the specific effectiveness of simple reminiscence by comparing it to conversation on current events, clinically depressed residents will not be included in the trial. More specifically, we will examine four hypothesis. Hypothesis one is that we expect an improvement of self-esteem, evaluated through the Rosenberg Self-Esteem Scale [15], in the experimental group by the end of the protocol when compared to the control group. Hypothesis two is that we expect an increase of life satisfaction, evaluated through the Life Satisfaction Index [16], in the experimental group by the end of the protocol when compared to the control group. Hypothesis three is that we expect an increase of the perceived quality of life, evaluated through the WHOQOL-Old Scale [17], in the experimental group by the end of the protocol when compared to the control group. Finally, hypothesis four is that we expect a decrease of depressive symptoms, measured through the Geriatric Depression Scale (GDS) [18], in the experimental group by the end of the protocol when compared to the control group. Further, we will assess whether these expected improvements in mental health and psychological well-being are maintained during a three-month follow-up period.

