**CONSORT flow diagram.**

### Sample size calculation

The number of participants was calculated in order to have a sufficient size to prove the effect of training, reducing type two (false negative) statistical errors. The limit of 0.05 will be used for type one errors (false positive).

Sample size calculation used an assumption that participants in the experimental group would report improvements, based on outcome over time, and that these effects would differ from those achieved in the control group. As noted in the introductory section, previous evaluations of this kind of reminiscence intervention have produced moderate effect sizes [20, 21]. Accordingly, we estimated a sample size for a moderate treatment effect over time. We calculated sample size by using a repeated-measures analysis of variance across time (pre-post) with an α level set at 0.05 (two-tailed), statistical power level (1-β) of 0.80, and an estimate of correlation among repeated measures of 0.5. The calculation, based on GPower 3 (Heinrich-Heine-Universität, Düsseldorf, Germany) [22], led us to estimate minimum sample size of 40 participants (or 20 per group).

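### The 80% power claimed for a moderate effect with 20 per arm corresponds to a between-arm difference in change of about 0.91 SD, close to what the article itself calls large

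*Protocol article*

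**What the plan says.** The section Sample size calculation first supposes that the experimental group will improve over time and that its improvement will differ from that of the control group, so the contrast of interest is group by time. It takes the size of the effect from earlier evaluations and refers back to the introduction: "Accordingly, we estimated a sample size for a moderate treatment effect over time". The inputs follow. The test is described thus: "We calculated sample size by using a repeated-measures analysis of variance across time (pre-post"). Alpha is 0.05 on two sides and the target power is 0.80. For the link between the two visits the authors enter "an estimate of correlation among repeated measures of 0.5". The software calculation "led us to estimate minimum sample size of 40 participants (or 20 per group").

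No numerical effect size appears in the section, and it does not say whether moderate refers to Cohen's f or to a standardized mean difference.

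The introduction does offer a scale. Under Reminiscence therapy, one meta-analysis is reported with d = 1.00 and described as a large effect. The more recent one is summarised by saying that "reminiscence interventions produced small to moderate improvements of depressive symptoms", with g = 0.57. The same review is quoted at g = 0.50, 0.52 and 0.73 for other indicators.

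**The concern.** The effect size decides what the power statement means, and it is the one input left without a value. The word moderate stands for different quantities on different scales. The conventional medium f of 0.25 for a two-group, two-visit interaction is twice as large, as a between-arm difference in change, as the conventional moderate d of 0.5. A reader who follows the pointer to the introduction, where effects are given as d and g, will take the trial to have 80% power for a difference of roughly half an SD.

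If that is not so, the trial is presented as adequately powered for effects of the size its own introduction reports when it is more likely than not to miss them.

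**Working it through.** **Inputs from the article.** Two-sided alpha 0.05; power 0.80; m = 2 visits; correlation rho = 0.5; k = 2 groups; N = 40, 20 per group. **Input not in the article:** the numerical effect size.

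**1. Trying to reproduce 40.** For the group-by-time test the noncentrality is lambda = f² × N × m / (1 − rho), referred to a noncentral F on 1 and N − 2 degrees of freedom. With the conventional medium f = 0.25:

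| Test | N for 80% power | Power at N = 40 |
|---|---|---|
| Group by time, 2 visits | 34 | 0.869 |
| Time (within factor), 2 visits | 34 | 0.869 |
| Group by time, 3 visits | 28 | 0.935 |
| Between groups, 2 visits, lambda = f² × N × m / (1 + rho) | 98 | 0.429 |

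None gives 40. Several unstated choices do: f of about 0.23 at correlation 0.5; f = 0.25 at correlation 0.4; or 34 inflated for 15% loss (34 / 0.85 = 40). The article does not let the reader choose among them.

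**2. What effect N = 40 can detect.** Solving the group-by-time test for 80% power at N = 40 and correlation 0.5 gives f = 0.227.

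**3. Translating f into SD units.** Let D be the between-arm difference in mean change, in units of the SD at a single visit. In a 2 × 2 layout each cell departs from additivity by D/4, so f = D/4.

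- f = 0.227 is D = 4 × 0.227 = 0.91 SD.
- f = 0.25 is D = 1.0 SD.
- D = 0.5 SD is f = 0.125.
- D = 0.57 SD is f = 0.1425.

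Check by the two-sample route: SD of change = sqrt(2 × (1 − 0.5)) = 1.0 SD, so lambda = D² × 20 / 2 = 10 D². The first formula gives (D/4)² × 40 × 2 / 0.5 = 10 D², which is the same.

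**4. Power at 20 per arm (F on 1 and 38 df).**

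| D | lambda = 10 D² | Power | Total N for 80% |
|---|---|---|---|
| 0.50 SD (assumed) | 2.50 | 0.338 | 128 |
| 0.57 SD | 3.25 | 0.420 | 100 |
| 0.73 SD | 5.33 | 0.614 | not computed |
| 0.909 SD | 8.26 | 0.80 | 40 |
| 1.00 SD | 10.0 | 0.869 | 34 |

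The normal approximation gives 0.352 and 0.437 in the first two rows, so the result does not depend on the method.

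**5. Does a more efficient analysis rescue the claim?** Adjusting for baseline at correlation 0.5 multiplies the SD by sqrt(1 − 0.25) = 0.866. Then 80% power is reached at 0.787 SD, with power 0.429 at 0.5 SD and 0.527 at 0.57 SD. If the correlation were 0.7 (an assumption more favourable than the article's), baseline-adjusted power would be 0.578 and 0.691. All remain below 0.80.

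**The case against.** The strongest reply is that the calculation may be sound on its own scale. With f = 0.25 and every stated input, 40 participants give 87% power and only 34 are needed, so any discrepancy is on the safe side. This stands. A reader might infer an arithmetic error, or that the correlation really used must have been 0.4. The article supports neither, because f of about 0.23 at the stated correlation also gives 40, as does 34 inflated for 15% loss.

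It is also fair to say that 0.5 SD is not the article's figure. Moderate is never quantified, and the evaluations cited for it are not available here. That limits the 34%. It does not remove the point, because the introduction to which the section refers supplies 0.57, and power there is 42%.

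Two further inferences go too far. One is that the article concedes smaller effects against its own comparator. The Aim of the study does report that one review "observed larger improvements in positive wellbeing if the control condition received no intervention as compared to standard conversation", but it also calls the evidence inconclusive and cites another review that found no significant difference between active-placebo and wait-list studies. The other is that a null result will be read as equivalence to conversation. The four hypotheses are all of superiority, and the article says nothing about how a null result would be interpreted.

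Finally, a condensed article may leave detail to other documents. Here, however, it states the test, alpha, power, correlation and N itself, and these do not fit a moderate effect on the scale that its introduction uses.

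**Conclusion.** The point holds as a fault in specifying the effect size. At the article's own alpha, correlation, pre-post design and N, 80% power is reached at a between-arm difference in change of about 0.91 SD. The article labels d = 1.00 large and g = 0.57 small to moderate, so the detectable difference lies near the upper label. Power is about 42% at 0.57 SD and about 34% at 0.5 SD.

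The figures assume that the test is group by time, as the section's description of the contrast implies, and that the introduction's d and g can be read as between-arm differences in SD units. The 34% further assumes that moderate means 0.5 SD. All figures take 20 analysed participants per arm; losses without replacement would lower them.

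**What to change.** Keep N = 40 and rewrite the end of Sample size calculation:

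- Give the effect size as a number, name its metric (f or standardized mean difference) and name the test (for example the group-by-time interaction), so that the listed inputs return 40. If 40 includes an allowance for loss, say so.
- Restate the power, for example: *20 per arm gives 80% power for a between-arm difference in change of about 0.91 SD (about 0.79 SD with baseline adjustment at correlation 0.5), and about 34% to 42% power for 0.5 to 0.57 SD without baseline adjustment, before any dropout.*

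The cost is wording only. No extra participants are needed and nothing in the conduct of the trial changes; the power statement becomes less favourable.

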### Questionnaires

#### Screening

The intake session will use the following questionnaires: the Mini Mental State Examination [23] to assess the cognitive level and the Geriatric Depression Scale [18] to evaluate the depressive symptoms.

#### Outcome measures

For the assessment of group reminiscence outcome, we will administer several questionnaires at baseline, post-intervention, and three months post-intervention. The Life Satisfaction Index ([16]; Italian validation [24]) is a questionnaire used to assess satisfaction of life that includes 20 items with three possible answers of ‘yes’, ‘no’, or ‘do not know’. The Life Satisfaction Index covers feelings of wellbeing among older people to identify ‘successful’ aging; it includes components like joy, resilience, comparison between desired and achieved goals, positive view of the self, and mood tone. It is assessed by evaluating the individual’s way of facing daily activities, finding life meaningful, reporting a feeling of success, and a positive self-image. The Rosenberg Self-Esteem Scale ([15]; Italian validation [25]) is a questionnaire with 10 items in which the respondents will be asked to reflect on their current feelings. Self-esteem is measured through four-point Likert scales from ‘strongly disagree’ to ‘strongly agree’. The scale score ranges from 0 to 30, with a higher score indicating higher self-esteem. Scores between 15 and 25 are within the normal range and scores below 15 indicate low self-esteem.

The WHOQOL-Old [17] questionnaire measures the perceived quality of life, with 24 items assessing various aspects of the quality of life, using five-point Likert scales. The scale is split into six subscales which explore different aspects: sensory abilities, autonomy, past, present and future activities, social participation, death and dying, and intimacy. The Geriatric Depression Scale ([18]; Italian adaptation [26]) evaluates the presence of depressive symptoms among older adults. It is composed of 30 items with possible answers of ‘Yes’ or ‘No’. One point is given to each answer based upon a scoring grid, and then the cumulative score is calculated. The simplicity of this scale is appropriate for older adults. The Reminiscence Function Scale [27] is only for the experimental condition. This questionnaire includes 43 items investigating the main functions and purposes of the reminiscing activity over the life course using six-point Likert scales. Seven factors have been identified: boredom reduction, death preparation, identity and problem-solving, conversation, intimacy maintenance, bitterness revival, and teach and inform.

### Data collection

Therapists (clinical psychologists) will record psychological data from each individual for the entire study. Security and privacy issues will be addressed according to the respective situation and the consent of the participant. Questionnaires will be collected at the end of all the scheduled sessions and at the three-month follow-up.

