**Methods/Design:**

We have designed a randomized controlled trial aimed at comparing the effects of group reminiscence therapy with those of group recreational activity on the psychological wellbeing of an institutionalized sample of older adults. The study includes two groups of 20 hospitalized elderly participants: the experimental group and the control group. Participants included in the experimental group will receive six sessions of group reminiscence therapy, while the control group will participate in a recreational group discussion. A repeated-measures design will be used post-intervention and three months post-intervention to evaluate changes in self-reported outcome measures of depressive symptoms, self-esteem, life satisfaction, and quality of life from baseline.

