### Trial design

In order to study the efficacy of the group reminiscence intervention, a between-subjects design will be used, with two experimental conditions and repeated measures across baseline, post-intervention, and three months post-intervention. Specifically, we will compare the following conditions. Experimental group: individuals will participate in group reminiscence meetings dealing with specific phases of their lives; they will share their memories and listen to the ones related by the other participants. Control group: individuals will participate in group conversations about current events.

Informed consent will be obtained from each participant. Psychometric outcomes will serve as quantitative dependent variables.

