### Randomization

The present study is a randomized controlled trial. Participants will be randomly assigned to one of the two groups of the trial, balanced on gender and pre-test scores.

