### Setting

The guidelines reported in group reminiscence literature [28] will be followed to structure our reminiscence intervention. Each meeting will include six participants and last 60 minutes. Two clinical psychologists will lead the sessions. The physical setting will be in the nursing home; a comfortable room will be provided, accessible to wheel-chairs, and participants will sit in a circle. The facilitating psychologists will encourage involvement of each participant, in order to stimulate the discussion or debate in a positive atmosphere. Personal criticism, moral judgments, and political statements will be averted. The detailed protocol is described below, for both the experimental and the control group.

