#### Control group

Every meeting will offer topics for discussion taken from newspaper and newscasts. Personal opinions will be promoted, and links with the daily life of participants will be welcome (everyday activities and personal preferences). A group discussion about these various themes will take place in every meeting from the first to the sixth. The main goal is to stimulate social interaction and communication, without discussing either personal events from the past or private memories. Final individual meetings will be scheduled for participants in both groups in order to administer the questionnaire and collect feedback from the users.

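### Therapists record the self-reported outcomes, and the final questionnaires share a meeting with programme feedback, so post-baseline scores are open to differential reporting bias of unknown size

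*Protocol article*

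**What the plan says.** The Data collection section of the protocol article names who handles the outcome data: "Therapists (clinical psychologists) will record psychological data from each individual for the entire study". On timing it adds: "Questionnaires will be collected at the end of all the scheduled sessions and at the three-month follow-up".

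The Setting section, which introduces both arms, says of delivery: "Two clinical psychologists will lead the sessions".

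The Control group section closes with a sentence that covers both arms: "Final individual meetings will be scheduled for participants in both groups in order to administer the questionnaire and collect feedback from the users". It does not say who conducts these meetings.

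The abstract describes the endpoints as "changes in self-reported outcome measures of depressive symptoms, self-esteem, life satisfaction, and quality of life from baseline", and Trial design gives them their role in the analysis: "Psychometric outcomes will serve as quantitative dependent variables". The Randomization section places baseline before allocation: "Participants will be randomly assigned to one of the two groups of the trial, balanced on gender and pre-test scores".

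**The concern.** The trial is meant to separate the specific effect of reminiscence from that of ordinary group conversation. A reporting shift that differs between arms cannot be told apart from that effect, and a larger sample would not remove it. Every endpoint named in the four hypotheses is self-reported, so no objective measure is available as a check.

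The article gives grounds for thinking that a shift could differ by arm:

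- All four hypotheses in Aim of the study predict benefit from reminiscence, and the comparator is described there as a placebo. Staff know which arm is expected to do better.
- Experimental participants share autobiographical memories under an assurance of confidentiality, while the control discussions keep away from private memories. Rapport with the psychologists could therefore differ, although the article offers no evidence that it does.
- Under Outcome measures, the Reminiscence Function Scale is given only in the experimental arm, so that arm's questionnaires point to the purpose of the study.

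This is a stated procedure and not a detail left to a fuller document. The article positively assigns recording to the therapists and positively combines the questionnaire with feedback.

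**Working it through.** **Step 1. What the sections establish together.**

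| Question | Source | Answer |
|---|---|---|
| Who records outcomes? | Data collection | Therapists, identified as clinical psychologists, throughout the study |
| Who delivers sessions? | Setting | Two clinical psychologists |
| Are the recorders aware of the arm? | The two above | Yes on a plain reading (shared title, and the word therapists) |
| Who runs the final meeting? | Control group | Not stated |
| Is it face to face? | Control group | Not stated; inferred from an individual meeting at which a questionnaire is administered |
| Are scales or feedback first? | Control group | Order not fixed; the questionnaire is named first |
| Is there feedback at three months? | Control group, Data collection | Not stated; therapist recording covers this time point |
| Is baseline exposed? | Randomization | No, because pre-test scores are used in the allocation |

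The first three rows support the point. The next four mark where inference begins. The last limits the point to the post-intervention and three-month scores.

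**Step 2. Illustration of size.** The plan gives no figure for reporting bias, so there is none to reproduce. From Sample size calculation I take 20 per arm, two-sided alpha 0.05 and a correlation of 0.5 between repeated measures. The shift b is my assumption.

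- SD of a pre-post change: σ√(2(1 − ρ)) = σ√(2 × 0.5) = σ. A shift of b SD in the post score is therefore also b SD on the change scale.
- Test: two-sample t on change scores, df = 20 + 20 − 2 = 38. This is equivalent to the group-by-time test with two time points.
- Noncentrality with no true effect: δ = b / √(2/20) = b / 0.316.
- Rejection rate: P(T > t₀.₉₇₅,₃₈) + P(T < −t₀.₉₇₅,₃₈), with T noncentral t (38 df, δ).

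| Assumed shift b (SD) | δ | Two-sided rejection | Rejection favouring reminiscence |
|---|---|---|---|
| 0 | 0 | 5.0% | 2.5% |
| 0.1 | 0.32 | 6.1% | 4.9% |
| 0.2 | 0.63 | 9.5% | 9.0% |
| 0.3 | 0.95 | 15.2% | 15.0% |

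The last column takes the shift to favour reminiscence. The rates are for one endpoint. They show how a 40-person trial responds to a given shift, not how large the shift is.

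**The case against.** The strongest reply is symmetry. The comparator is an active, psychologist-led group with the same final meeting, so a wish to please the staff would act in both arms and largely cancel in the contrast. That stands: only the differential part matters.

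The second reply is that recording is not rating. The scales have fixed responses, the depression scale is scored from a grid, and the article speaks of questionnaires being collected. Participants may fill in the forms themselves while psychologists merely gather and enter them. That also stands, and it narrows the likely route to how the scales are administered and answered.

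Three stronger readings are tempting and are not supported:

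- A reader might infer that participants answer mood and self-esteem items face to face to the person who led their own group. No section says this. With six participants per meeting and 20 per arm (20/6 ≈ 3.3) there must be more than three groups in each arm, and the article does not say whether the same two psychologists lead them all.
- A reader might infer that feedback comes before the scales or is mixed with them. The text names the questionnaire first, so the safer order may already be intended; it is simply not fixed.
- A reader might infer that every measurement is compromised. Baseline is not, and the shared feedback meeting is documented for one contact only.

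What these replies do not answer is that recording is expressly given to therapists, and that nothing in the article separates outcome collection from delivery or from feedback on the programme.

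**Conclusion.** The point holds in a limited form. The article states a measurement procedure prone to bias: outcome recording by therapists who, on a plain reading, know the arm, and a final meeting that serves both measurement and programme feedback. With four self-reported outcomes and hypotheses that all point the same way, the post-intervention and three-month contrasts are exposed to differential reporting bias.

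Its size is unknown. The rise from 5% to about 6%, 10% or 15% rests on assumed shifts of 0.1, 0.2 or 0.3 SD and must not be read as the trial's actual error rate. The conclusion assumes that the therapists of Data collection are the psychologists of Setting, which the wording favours but does not prove. The matter merits an amendment because the remedy needs no new staff or visits; it does not show that a result of this trial would be wrong.

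**What to change.** Amend Data collection and the closing sentence of the Control group section so that, in both arms alike:

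1. Participants complete the four scales themselves where able, before any discussion of the programme.
2. Forms are returned sealed and scored under a study code that does not reveal the arm.
3. Reading help follows a neutral script and, where staffing allows, comes from a psychologist who did not lead that participant's group. If the same two psychologists lead every group this safeguard is unavailable, and the article should say so.
4. The mode of completion and any assistance are recorded at each assessment.
5. The article states who conducts the final meeting and the three-month contact.

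An analysis without assisted forms should be a sensitivity analysis only: needing help at follow-up is a post-randomisation feature, and dropping those forms shrinks an already small sample.

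The cost is revised procedures, printing and probably a few more missing items. According to Trial status, recruitment began in October 2012 and was still open. Participants already enrolled may therefore have baseline and follow-up scores from different modes, which is why the change must apply equally to both arms and the mode be recorded. The sample size does not change. Some bias will remain, because participants know which programme they attended.
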